## Abstract

**Background:**

Stroke is a major cause of death and disability in the world, and the prevalence of stroke tends to increase with age. Despite advances in acute care and secondary preventive strategies, primary prevention should play the most significant role in the reduction of the burden of stroke. As an important component of traditional Chinese *Qigong*, *Baduanjin* exercise is a simple, safe exercise, especially suitable for older adults. However, current evidence is insufficient to inform the use of *Baduanjin* exercise in the prevention of stroke.

The aim of this trail is to systematically evaluate the prevention effect of *Baduanjin* exercise on ischemic stroke in the community elder population with high risk factors.

**Methods:**

A total of 170 eligible participants from the community elder population will be randomly allocated into the *Baduanjin* exercise group and usual physical activity control group in a 1:1 ratio. Besides usual physical activity, participants in the *Baduanjin* exercise group will accept a 12-week *Baduanjin* exercise training with a frequency of five days a week and 40 minutes a day. Primary and secondary outcomes will be measured at baseline, 13 weeks (at end of intervention) and 25 weeks (after additional 12-week follow-up period).

**Discussion:**

This study will be the randomized trial to evaluate the effectiveness of Baduanjin exercise for primary prevention of stroke in community elder population with high risk factors of stroke. The results of this trial will help to establish the optimal approach for primary prevention of stroke.

**Trial registration:**

Chinese Clinical Trial Registry: ChiCTR-TRC-13003588.

Registration date: 24 July, 2013.

## Background

Stroke, about 87% being ischemic [1], causes 9% of all deaths around the world and is the second most common single cause of death after ischemic heart disease, with over five million deaths per year globally [2]. Stroke is also the most common cause of disability, with 20% of survivors requiring institutional care after three months and 15 to 30% being permanently disabled [3]. In Europe, it is estimated about that 250,000 people become disabled after their first stroke each year [4]. Stroke consumes about 2 to 4% of total healthcare costs in the world, and accounts for more than 4% of direct healthcare costs in industrialized countries [5]. In China, approximately 1.5 to 2 million new strokes occur each year, and 15 to 30% of them are permanently disabling [6]. The economic burden is estimated at a total annual cost of about ten billion yuan [7]. Although acute treatment is essential in reducing recurrences and disability, primary prevention plays the most significant role in the reduction of the burden of stroke [8]. Therefore, it is important to make efforts to prevent stroke rather than just treat stroke.

Stroke is multi-factorial in causation. Over 100 risk factors, which can be classified as non-modifiable or modifiable, have been identified as likely contributors to its pathogenic progression [9]. The most effective means available for stroke prevention involve modification and treatment of risk factors which mainly include high blood pressure, high cholesterol, high blood glucose, diabetes, certain other cardiac conditions, dyslipidemia, physical inactivity, obesity and so on [10-12]. It has been estimated that over 50% of stroke are preventable through control of modifiable risk factors [13]. For example, lowering blood pressure can reduce an approximate 30 to 40% of the risk of stroke [14,15]; furthermore, 17% further risk reduction may be obtained by reducing the serum concentration of LDL-cholesterol [16]. Nevertheless, despite drug therapies for many of these risk factors being available [17], they remain a limitation because of their high costs, unpredictable side-effects and most subjects having multiple risk factors. Therefore, this task remains a challenge for societies, healthcare and financial systems.

The increasing evidence indicates that exercise and regular physical activity are associated with a reduced risk of stroke through controlling weight and blood pressure, reducing glucose, and modifying lifestyle [18,19], but the precise amounts and type of exercise required to prevent stroke still are unclear [20]. Although intensive forms of physical activity can provide additional protection benefits for stroke, the prevalence of such activities in older people is quite low [21]. As an important component of traditional Chinese *Qigong* exercises, *Baduanjin* exercise is an ancient art and science of healthcare that has been practiced in China for thousands of years [22]. It is a combination of postures, meditation and movements designed to improve holistic health and to achieve the integration of mind and body [23-26]. It can exercise the movable joints and muscle in the whole body, enhancing respiratory function and at the same time modulating mind and spirit [27].

Many studies have demonstrated the beneficial effects of *Baduanjin* exercise on reducing blood lipids [28,29], lowering blood pressure [30], reducing blood sugar and glycosylated hemoglobin [31,32]. Recent review has proven the benefits of *Baduanjin* exercise on cardiopulmonary function and body morphology [33]. Additionally, significant improvement has been reported in balance, strength and flexibility, as well as pain reduction and improvement in sleep quality, psychological well-being and immune function [34-36]. However, few studies are randomized trials, most have significant methodological limitations, and we are not aware of any trials that have evaluated the impact of *Baduanjin* exercise on primary prevention of stroke in the community elder population with high risk factors for stroke.

This study will adopt the strict randomized controlled design. The aim is to systematically evaluate the preventive effect of *Baduanjin* exercise on ischemic stroke in the community elder population with high stroke risk factors by observing the difference between a *Baduanjin* exercise group and a general physical activity group.

## Methods/Design

This is a two-arm, randomized, assessor blinded, parallel controlled trial. The primary aim is to assess the effect of *Baduanjin* exercise on risk factors for stroke in the community elder population.

This trial will be performed at Wufeng Community Center, in Gulou District, Fuzhou City, China. A total of 170 eligible participants will be randomly allocated into intervention group (the *Baduanjin* exercise group) and control group (general physical activity group) in a 1:1 ratio. The participants in the intervention group will accept a 12-week *Baduanjin* exercise training, at the same time the others in the control group will maintain their original physical activity. Primary and secondary outcomes will be measured at baseline, end of 12-week intervention and after an additional 12-week follow-up period by the assessors who are not involved in this trial at the Affiliated Rehabilitation Hospital, Fujian University of Traditional Chinese Medicine. The statistic analysis will be performed by a statistician at the Center of Evidence Based Medicine, Fujian University of Traditional Chinese Medicine. A flow diagram of this trial is shown in Figure 1.

**Figure 1 F1:**
[figure not shown]
Flow diagram of study design.

### Sample size

Sample size computation is based on the changes in cerebral vascular hemodynamic parameter between comparison groups with a 5% per comparison significance level and a two-tailed critical region. The mean and SD of cerebral vascular hemodynamic parameter in the control group as obtained from relevant literature are 32.0 and 6.0 respectively [37]. We expect a 10% mean improvement of this outcome after 12-week *Baduanjin* exercise intervention. A total of 170 participants is calculated as needed to detect the target effect size with 90% power. In order to avoid excessive loss to follow-up, we will illustrate in detail to the participants the potential health benefits of *Baduanjin* exercise. For completeness of whole trial progress we will also provide confidence incentives to participants. Furthermore, we will collect information from participants in both the *Baduanjin* exercise and the usual physical activity control group regarding the likelihood that they will drop out. This information will be used to attempt to reduce the incidence of drop-out.

### Participants and recruitment

#### Eligibility criteria

##### Definition of people with high risk of ischemic stroke

According to ‘The 2012 annual screening and intervention project “Workbook of Stroke High Risk Population”’, the participants with high risk of ischemic stroke should meet two of following items (1) to (7) or item (8): (1) have a history of high blood pressure (systolic/diastolic pressure ≥ 140/90 mmHg), or be taking antihypertensive drugs; (2) have atrial fibrillation; (3) smoke (at least one cigarette each day for one year); (4) have dyslipidemia; (5) have diabetes mellitus; (6) be obviously overweight or obese (BMI ≥ 24 kg/m^2^); (7) have a family history of stroke (a stroke history in three generations); (8) have a history of transient ischemic attack (TIA).

### Inclusion criteria

The eligible participants must meet all the following criteria: (1) be confirmed as people with high risk of ischemic stroke; (2) have not conducted regular physical exercise for at least one year (regular exercise means lasting more than three months with a frequency of three to four times a week and at least 30 minutes per session); (3) be male or female aged from 50 to 70 years old; (4) have signed the informed consent document.

### Exclusion criteria

The eligible participants should not meet any of the following criteria: (1) have a history of stroke; (2) have been suffering from severe cerebrovascular disease, musculoskeletal system diseases, or other sports injury related contraindications; (3) have a communication disorder, such as dementia or mental disorder.

### Recruitment

The participants’ recruitment will be performed at Wufeng Community Center in Gulou district, Fuzhou city. We will recruit the eligible participants through posting-up posters, sending leaflets, and setting a recruiting station in the community center. The potentially eligible subjects who are interested in this study can then contact the recruiters. The eligible subjects will be included if they are in accordance with the inclusion criteria and not meeting any of the exclusion criteria.

### Randomization and allocation concealment

The eligible participants will be randomly allocated in a 1:1 ratio to either *Baduanjin* exercise group or the usual physical activity group. The random allocation sequence will be generated using the statistical software SAS 9.1 by a statistician who will be not involve in this trial at the Center of Evidence Based Medicine, Fujian University of Traditional Chinese Medicine. The random allocation sequence will be managed by the project manager who is not involved in the recruitment program. The eligible participants will be informed of their allocation result by the project manager via telephone after their baseline information has been assessed.

### Blinding

Although it is impossible to blind the participants and exercise coaches due to this being a non-pharmacological intervention trial, two kinds of blind code will be used to blind the outcome assessors and statistician, and will be kept by a project manager who will be involved in the recruitment, intervention, assessment, and statistical analysis procedure of this trial. The participants’ allocation result (the *Baduanjin* exercise group or usual physical activity group) will be replaced by using alphabet ‘A’ or ‘B’ in the first blind code, and the real meaning of ‘A’ or ‘B’ will be marked in the second blind code.

A twice unclosed blind code will be performed in this trial. Firstly, after close of data-base, the project manager will deliver the group code ‘A’ or ‘B’ of participants to the statistician. Secondly, the project manager will declare the real meaning of group ‘A’ or ‘B’ after analysis of all data is completed.

### Intervention

#### Baduanjin exercise group

The participants in the *Baduanjin* exercise group will receive a 12-week *Baduanjin* exercise training with a frequency of five days per week and 40 minutes per day. Eighty-five participants will be freely gathered into three training units with 25 to 30 people per training unit, and the *Baduanjin* exercise training will be performed at Wufeng Community Center. We will employ three professional coaches, who have engaged in teaching the college students physical education at the Fujian University of Traditional Chinese Medicine for at least five years, to guide participants’ training. The training scheme of *Baduanjin* exercise originated from the ‘*Health Qigong Baduanjin Standard’* enacted by the State Sports General Administration in 2003 [38]. The whole set of Baduanjin exercise consists of ten postures (including the preparation and ending posture) (Figure 2) [39]. Two supervisors will be in charge of the management of each training site to guarantee the quality of Baduanjin exercise training.

**Figure 2 F2:**
[figure not shown]
Ten postures of Baduanjin exercise.

### Usual physical activity group

Participants allocated to the control group will not receive any specific exercise training from the study scheme. They will be requested to maintain their original habit of physical activity.

In order to exclude bias from the exceed activity of participants, all participants in both groups will be required to record an activity log in the intervention period, in which the duration and intensity of their activity or exercise in a whole day will be classified into three sections including the duration of low-intensity activity, the duration of moderate-intensity activity, and duration of high-intensity activities.

### Follow-up

After the 12-week intervention period, all participants will enter an additional 12-week unsupervised follow-up period. They will resume their original lifestyle in the follow-up period, but they will be required to record their activity log as in the intervention period. Two supervisors will investigate the quality of each activity log by telephone once every two weeks.

### Outcome assessment

The outcome assessment will be conducted at baseline (-2 to -1 weeks), end of intervention (13 weeks), and end of follow-up period (25 weeks).

The variables in this trial consist of basic characteristic variables, primary outcomes, and secondary outcomes. The basic characteristic variables will be measured at baseline (before randomized allocation); the primary or second outcomes will be measured at baseline, end of intervention period, and end of follow-up period, respectively. All outcome assessment will be independently performed by the assessors or operators who are blinded the allocation results of participants. A summary of all measurements in this trial is shown in Table 1.

**Table 1 T1:** Study flow chart

**Items**		**Before enrollment (weeks)**	**Intervention period (weeks)**	**End of the exercise (weeks)**	**Follow-up (weeks)**	**End of the follow-up (weeks)**
		**−2 to (-1)**	**1 to 12**	**13**	**13 to 24**	**25**
Recruitment		×				
Enrollment		×				
Inclusion criteria		×				
Exclusion criteria		×				
Informed consent		×				
Basic characteristic variables		×				
Randomization and allocation concealment		×				
Primary outcomes	Cerebrovascular function	×		×		×
	Cardiopulmonary function	**×**		**×**		**×**
Secondary outcomes	Motor function	**×**		**×**		**×**
	Physical parameters	**×**		**×**		**×**
	Blood lipids	**×**		**×**		**×**
	Fasting plasma glucose(FPG)	**×**		**×**		**×**
	Inflammation factors	**×**		**×**		**×**
	Quality of sleep	**×**		**×**		**×**
	Quality of life	**×**		**×**		**×**
	Happiness	**×**		**×**		**×**
	Emotion and mood	**×**		**×**		**×**
	Self-confidence and self-esteem	**×**		**×**		**×**
Adverse events recorded			×		×	
Activity log			×		×	

### Basic characteristic variables

Demographic characteristics will be collected by the recruiters through using a standardized questionnaire (gender, age, nationality, education level, occupation, marital status).

Information on stroke risk factors regarding smoking, drinking, height (cm), weight (kg), blood pressure, family history of stroke, blood lipids, and blood sugar will be gathered through medical records.

Other information including history of diseases, physical activity or exercise habits, and drug administration information will be collected by the recruiters through using a standardized questionnaire.

### Primary outcomes

Cerebrovascular function consists of cerebral vascular hemodynamic and cerebrovascular elasticity. Cerebral vascular hemodynamic parameters consist of the maximum blood flow velocity (Vmax), minimum blood flow velocity (Vmin) and mean blood flow velocity (Vmean). Those parameters from the vertebral, basilar, middle cerebral, anterior cerebral and posterior cerebral arterial territories of the brain will be measured using Color Doppler ultrasound imaging device (PHILIPS, product type: IU22) by the professional operators at the Affiliated Rehabilitation Hospital of Fujian University of Traditional Chinese Medicine. Cerebrovascular elasticity consists of the elasticity index (PI) and vascular resistance index (RI) of vertebral, basilar, middle cerebral, anterior cerebral and posterior cerebral arteries. It will be measured using Color Doppler ultrasound imaging device (PHILIPS, product type: IU22) by the professional operators at the Affiliated Rehabilitation Hospital of Fujian University of Traditional Chinese Medicine.

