### Statistical analysis

Statistical analyses will be performed using SPSS 21.0 (IBM, Chicago, IL, USA) software packages by a statistician, who is not involved in the outcome measurements, at Center of Evidence Based medicine, Fujian University of Traditional Chinese Medicine. The statistical significance is defined as two-sided *P* value of < 0.05. In descriptive analysis of the sample, the central tendency for the continuous variables will be expressed using mean (standard deviation) or median (interquartile range) for symmetrical distributions; normality will be tested using the Kolmogorov-Smirnov test. Appropriate transformations will be applied in cases of a non-normal distribution. The categorical variables will be expressed as proportions with their standard error. Statistical comparisons for the baseline characteristics, primary and secondary outcomes between groups will be compared using the Student’s *t-*test or Mann-Whitney *U*-test for continuous variables and the Pearson Chi-squared or Fisher exact test for categorical variables. Analysis of the primary and secondary outcomes will be on the basis of the intention-to-treat (ITT) population and per-protocol (PP) population. The result of the ITT analysis will be compared with that of the PP analysis to determine whether the results are consistent. Every effort will be made to minimize missing data and drop-out or loss to follow-up during the study period. Missing data will be filled by Bayesian methods. If the amount of missing data for primary outcome or potential confounders is substantial (that is > 10%), multiple imputation methods will be considered to perform the statistic analysis. Linear models or linear regression will be applied for dependent continuous variables and logistic regression models for dependent categorical variables if incomparability of baseline characteristics between groups appears. Subgroup analysis stratified by participants’ sex will be used for the primary outcomes. Analysis of variance (ANOVA) will be used for the repeated measurement data, and the *post hoc* comparison will be applied if the difference is found to be significant. Adverse events will be listed and analyzed using a Chi-squared or Fisher’s exact test. Severe adverse events will be listed in detail.

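### Twenty-five Doppler variables are primary, each tested at 5%, with no deciding variable or time point, so the family-wise error is well above 5% and the stated power covers one unidentified test

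*Protocol article*

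**What the plan says.** All references are to the protocol article.

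- **Primary outcomes** divides cerebrovascular function into two parts. For the first, "Cerebral vascular hemodynamic parameters consist of the maximum blood flow velocity (Vmax), minimum blood flow velocity (Vmin) and mean blood flow velocity (Vmean"; these are taken in the vertebral, basilar, middle, anterior and posterior cerebral territories. The second part is the "elasticity index (PI) and vascular resistance index (RI) of vertebral, basilar, middle cerebral, anterior cerebral and posterior cerebral arteries". No variable, artery or summary measure is singled out.
- **Outcome assessment** says that "the primary or second outcomes will be measured at baseline, end of intervention period, and end of follow-up period". The two post-baseline visits are at weeks 13 and 25, and neither is called primary.
- **Sample size** works at a "5% per comparison significance level and a two-tailed critical region". It uses one cerebral vascular hemodynamic parameter, unnamed, whose mean and SD "in the control group as obtained from relevant literature are 32.0 and 6.0 respectively". It expects a 10% improvement after the 12-week programme, gives no direction, and concludes: "A total of 170 participants is calculated as needed to detect the target effect size with 90% power".
- **Statistical analysis** uses one rule throughout: "The statistical significance is defined as two-sided" P below 0.05. For the outcomes it lists t or Mann-Whitney tests between groups. It also lists an ANOVA for repeated measurements, followed by post hoc comparisons if that is significant. It does not say which of these decides.

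**The concern.** A confirmatory trial needs one result, or a defined rule over several, that settles the primary question. Here 25 variables share primary status and each is judged at 5%. If a few of them reach significance and the others do not, the article gives no basis for saying whether the primary question was answered yes or no. The more variables that count equally, the likelier it is that one of them is significant by chance.

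The sample size does not resolve this. It was computed for one parameter, and the reader cannot tell which. At stake are the meaning of a significant primary finding and the meaning of the 90% power.

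**Working it through.** **1. Size of the family.** Three velocities plus two indices, in five arteries: (3 + 2) × 5 = 25 variables. The velocity measures alone number 3 × 5 = 15. If weeks 13 and 25 are tested separately, there are 25 × 2 = 50 comparisons. Table 1 also places cardiopulmonary function under primary outcomes, while the text lists it under Secondary outcomes; it is not counted here.

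**2. The plan's own sample size.** Inputs from the Sample size section: difference 10% × 32.0 = 3.2, SD 6.0, two-sided 5%, power 90%.

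n per arm = 2 × (1.960 + 1.282)² × 6.0² / 3.2² = 73.9, so 74 per arm and 148 in total. The t-based calculation gives 75 per arm, 150 in total.

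The stated 170 is not reproduced exactly. It would fit an unstated allowance of about 12% for dropout (170 to 172). It exceeds what the inputs require, so it is not an error on this point. What matters is that the calculation contains one comparison at 5%.

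**3. Power at the stated size.** With 85 per arm: 3.2 / (6.0 × √(2/85)) = 3.477, and Φ(3.477 − 1.960) = 0.935. The t-based value is 93.3%. This holds for one parameter at one time, with everyone analysed.

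**4. Family-wise error.** If the exercise has no effect, the expected number of significant results among 25 tests is 25 × 0.05 = 1.25, whatever the correlation. Under independence, the chance of at least one is 1 − 0.95²⁵ = 0.723; for 50 tests it is 1 − 0.95⁵⁰ = 0.923.

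The documents give no correlations, so a range is assumed. The values for correlated tests come from 200,000 simulated sets of normal test statistics with a common correlation.

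| Assumed common correlation | 25 tests | 50 tests (both visits tested separately) |
|---|---|---|
| 0 | 72% | 92% |
| 0.5 | 47% | 62% |
| 0.7 | 32% | 40% |
| 0.9 | 16% | 19% |

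Even at 0.9, the figure for 25 tests is more than three times 5%.

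**The case against.** Several points on the other side stand, and they limit how far the criticism goes.

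- A reader might infer that type I error is not controlled at all. It is: each test is held at 5%, and the Sample size section says openly that the level is per comparison. Only the family-wise rate is uncontrolled.
- A reader might infer that a chance finding is very probable. For 25 tests, only the independence figure in the table exceeds one half. Independence is implausible for velocities and indices taken from the same arteries in the same people. Well above 5% is what the figures support.
- The 50-test column is one reading, not the plan as written. The repeated-measures ANOVA, with post hoc comparison only after a significant result, is a gate across visits. Used alone, it would leave about 25 overall tests. The simple group tests are listed too, however, and precedence is not stated.
- A reader might say that the powered parameter matches nothing in the outcome list. That goes too far. The Sample size section uses the term that Primary outcomes defines as the three velocities, which excludes PI and RI. The mention of 12 weeks also points towards week 13. Fifteen candidates remain.
- The article states no success rule, so it does not expressly allow any single significant variable to be called a positive trial. An unseen analysis plan might also hold a multiplicity strategy, and its absence here is not the finding. The finding rests on what the article does fix: an undifferentiated primary list and 5% per comparison.
- The analysis by sex is labelled a subgroup analysis, and nothing is said about measuring left and right sides. Neither is counted.

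**Conclusion.** The point holds in this form. The primary outcome is 25 Doppler variables at two post-baseline visits, with no deciding variable or time and a two-sided 5% level for each comparison. Over the 25 variables, the family-wise error lies between about 16% and 72% for assumed common correlations from 0.9 down to 0. It is higher if the two visits are tested separately. The 90% power applies to one test on one of 15 possible velocity measures.

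The count and the 5% level come from the text. The equal-correlation model and its values are assumptions, but the conclusion does not change anywhere in the range. This needs correcting, because the stated rule and the stated list together can yield a misleading primary result.

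**What to change.** Amend the protocol to name one primary endpoint: the parameter and artery from which 32.0 and 6.0 were taken, at week 13. State the direction that counts as improvement and the one between-group test that decides. Make the other velocities, PI and RI, the other arteries and week 25 secondary, either with Holm or false-discovery-rate control or labelled exploratory.

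Timing matters. Under the Blinding section, the statistician receives the A/B codes after the database closes, and their meaning is declared only once all analysis is complete. A change made merely before that last step could follow sight of every A-versus-B result. The amendment should be made before any outcome data are seen by group, and in any case before the A/B codes are released.

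The cost is an amendment and a registry update in a trial that is already registered, ethics-approved and recruiting, and fewer parameters that can be claimed as primary. No extra participants are needed: 85 per arm gives about 93% power before dropout, and 90% is kept down to 75 analysed per arm, a loss of 10 per arm. Keeping all 25 as primary with a Bonferroni correction would cost far more. At a level of 0.05/25 = 0.002, power for the same effect would be Φ(3.477 − 3.090) = 65% at 85 per arm, and 90% would need 135 per arm, 270 in total.
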